### 6.2.3 Administration of study products

To prepare and administer study product, study sites and investigators must comply with any applicable regulations. The step-by-step instructions for the investigator (or delegated staff) are found in the Manual of Procedures.

## 6.3 Accountability Procedures for Study Products

The study products will be kept in a secure place in cold storage at the study site segregated from other products. During the study staff in charge of research product management will record information related to the delivery of study products to the trial site, conduct inventory at the trial site, check the number of doses given to the participants, check the number of unused or partially unused vials, and return these to Butantan after completing the study, if directed.

## 6.4 Assessment of Compliance with Use of the Study Products

Compliance with use of the study products will be closely monitored during the trial by the research team and trial monitors.

## 6.5 Concomitant Medications/Treatment

Concomitant medications will be documented throughout the course of the study.

Treatment of conditions that are not exclusionary should continue, if needed by the participant. Subsequent changes in concomitant treatment during the trial must also be reflected in the CRF.

Women included in the trial who are using hormonal contraception at the time of enrollment should continue using these products through 60 days after the last vaccine dose. Use of such products or any other methods of contraception must also be documented in the CRF. Condoms may be provided to all volunteers upon request.

## 6.6 Unauthorized Products

The following products are not authorized to be used during the study:

1. Any concomitant medicine or biologic specifically prescribed for the treatment of a condition which is an exclusion criterion for participation in the trial.
2. All non-study vaccines or biologics (including blood products).

Other concomitant products are allowed.

Participants will be requested not to take analgesic or antipyretic drugs *in a preventive way* (before or soon after injection)*,* as such medications might change the reactogenicity profiles of study vaccine and placebo.

# Study Schedule; Description of Visits

## 7.1 Screening/Triage (visit T)

Prior to inclusion into the vaccine study, each participant will be screened by means of multiple procedures, including laboratory testing, medical history interview and targeted physical examination. Because screening procedures are required to assess eligibility, they will be performed only after consent is obtained. The Principal Investigator or designee will record the identification of all participants who enter screening; whether they entered the trial or failed screening, and the reason for screen failure on the screening/enrollment log.

Screening visits can occur upto 30 days before V1 (first study injection).

After participants are consented, the following activities will occur:

1. The participant will be interviewed to collect baseline demographic data (date of birth or year of birth if specific date not known, gender, race/ethnicity, etc.).
2. A study clinician will interview the participant to collect a detailed medical history including concomitant medications. Study staff will review the information to confirm eligibility prior to conduct of further procedures.
3. A study clinician will perform a targeted physical examination. Results will be reviewed by study staff and with the participant to confirm eligibility prior to conduct of further procedures. If a person is considered ineligible based on medical history and physical examination, the study clinician will tell the person that he or she is not eligible, the reasons will be explained and referral for appropriate care made if necessary.
4. Blood (serum and whole) specimens will be collected for biochemical and hematological testing. Serum specimens will also be collected for testing for chronic viral hepatitis infections as well as HIV. Specimen collection information must be documented in the relevant source documentation. About 17,5 mLs of blood will be collected.
5. For women, a urine pregnancy test will be done.
6. Study staff will instruct the participant on when to return for screening results and possible enrollment into the study.

## 7.2 Study Injections and Follow-up Periods

### 7.2.1 Day of Study Injection (V1)

Visit V1 is the day of injection of study product. It can occur up to 30 days after the screening visit.

1. Study staff will confirm participant identity.
2. A study clinician will review results of all screening laboratory testing with the participant. Appropriate referrals will be conducted for any abnormalities. All results will be reviewed to confirm eligibility prior to conduct of further procedures.
3. Study staff will inquire about any new medical events since medical histories were recorded and confirm eligibility prior to conduct of further procedures.
4. A study clinician will perform a targeted physical examination if necessary. Results will be reviewed by study staff and with the participant to confirm eligibility prior to conduct of further procedures.
5. Women will have a urine pregnancy test to confirm there is no pregnancy on the day of vaccination.
6. Eligibility is confirmed after the revision of inclusion/exclusion criteria and recorded on the study CRF.
7. A study clinician will review the study procedures with each eligible participant.
8. Prior to administration of study product, a blood specimen will be collected by venipuncture from the participant’s **dominant arm** preferably for anti-influenza serologic assays. Specimen collection information must be documented on the CRF and in specimen collection logs. About 30 mLs of blood will be collected.
9. The person in charge of performing the injection will confirm that the study product about to be injected is labeled with the correct participant identification.
10. The participant will be administered one injection of the investigation product in the deltoid muscle of the non-dominant arm.
11. The participant will be observed for 30 minutes after administration. Local and systemic reactions occurring in the first 30 minutes will be recorded.
12. The participant will be given a Participant Diary, a digital thermometer and a local reaction measurement devicein which the participant will be asked to record any local and/or systemic reactions that might appear within 7 days post vaccination, and record any concomitant medications. The participant will be instructed how to use the Participant Diary, thermometer and a local reaction measurement device. All relevant explanations should be included in the Participant Diary. The Participant Diary will also have contact information for the investigators, should the participant have any questions. The participant will be informed that a member of the investigator’s team will call on V1+3 to check on the participant’s completion of the Participant Diary and participant’s well-being.
13. The participant will be instructed that if the participant experiences an AE requiring medical care, the participant should inform the study staff as soon as possible and seek medical care as appropriate. If the participant visits a health care provider, the participant should be sure to inform the health care provider of participation in this study and provide the health care provider with the investigator’s contact information.

### 7.2.2 First Week after Study Injection (contact C1)

1. The participant will complete the Participant Diary daily, reporting any local or systemic reactions, daily temperature and medications taken.
2. The participant will have been instructed that if he/she experiences an AE requiring medical care, the participant should inform the study staff as soon as possible and seek medical care as appropriate. If the participant visits a health care provider, the participant should be sure to inform the health care provider of participation in this study and provide the health care provider with the investigator’s contact information.
3. Three days after study injection (V1+3) study staff will call the participant (contact C1) to check that the participant is correctly completing the Participant Diary and to check on the participant’s well-being. If any concern arises from the safety assessment over the phone the participant will be directed to come to the study site.

### 7.2.3 Seventh Day after Study Injection (visit S1)

1. Study staff will confirm participant identity.
2. Study staff will review the Participant Diary and interim history with the participant and inquire about any new medical events since medical histories were last updated. Any AEs that have occurred will be recorded in the appropriate CRFs.
3. A study clinician will perform a targeted physical examination and record the information on the CRF. Results will be reviewed by study staff and with the participant and any AEs that have occurred will be recorded in the appropriate CRF.

Blood specimens will be collected for testing selected biochemical parameters (total bilirubin, ALT, AST, creatinine) and selected hematologic studies (WBC, Hgb, and platelets). Specimen collection information must be documented on the CRF and in specimen collection logs. About 9 mLs of blood will be collected.

1. Laboratory results will be reviewed within 36 hours of receipt by the study physician. Any out-of-normal-range result Grade 2 and above will be evaluated by the study physician to assess whether it is of clinical significance and whether it is related to vaccination. Laboratory results that are Grade 2 or above and considered to be clinically significant will be followed by the study clinician until resolution or stabilization.
2. The participant will be instructed to inform the study staff as soon as possible if he/she experiences an AE requiring medical care and to seek medical care as appropriate. If the participant visits a health care provider, the participant should be sure to inform the health care provider of participation in this study and give the health care provider the contact information for the investigator. Study staff may request to review any document related to participant´s visits or hospitalizations handed to study staff by participants (e.g.: hospital discharge summaries, etc), and considered relevant to the assessment of potential adverse events, and if permitted by the participant, extra information may be requested by study staff to other health care services/providers.

### 7.2.4 Second and Third weeks after Study Injection

There are no scheduled visits during this period. Participants may be asked to come to the study clinic if the investigator follows up on any laboratory or clinical issue. The participant will inform the study clinic of any medical events and seek medical care as needed. The participant will be instructed to give any health care provider they see the contact information for the investigator.

### 7.2.5 Immunogenicity Visit and Second Study Injection (visit V2)

The Visit V2 is scheduled 28 days after V1 for collection of immunogenicity samples for the study and to administer the second dose of vaccine or placebo.

1. Study staff will confirm participant identity.
2. Eligibility criteria will again be reviewed
3. Study staff will review interim medical histories, including any unsolicited AE and concomitant medications with the participant since these were last updated. Results will be recorded in the appropriate section of the CRFs.
4. Women will have a urine pregnancy test to confirm there is no pregnancy on the day of study injection.
5. Prior to administration of study product, a blood specimen will be collected by venipuncture from the participant for immunogenicity testing. Specimen collection information must be documented on the CRF and in specimen collection logs. About 40 mLs of blood will be collected.
6. The person performing the injection will confirm that the study product about to be injected is labeled with the correct participant identification.
7. The participant will be administered one injection of study product in the deltoid muscle of the non-dominant arm.
8. The participant will be observed for 30 minutes after administration. Local and systemic reactions occurring in the first 30 minutes will be recorded.
9. The participant will be given a Participant Diary, a digital thermometer and a local reaction measurement devicein which the participant will be asked to record any local and/or systemic reactions that might appear within 7 days after V2, and record any concomitant medications. The participant will be instructed how to use the Participant Diary, thermometer and a local reaction measurement device. All relevant explanations should be included in the Participant Diary. The Participant Diary will also have contact information for the investigators, should the participant have any questions. The participant will be informed that a member of the investigator’s team will call on visit V2+3 to check on the participant’s completion of the Participant Diary and participant’s well-being.
10. The participant will be instructed that if the participant experiences an AE requiring medical care, the participant should inform the study staff as soon as possible and seek medical care as appropriate. If the participant visits a health care provider, the participant should be sure to inform the health care provider of participation in this study and provide the health care provider with the investigator’s contact information.

### 7.2.6 First Week after second Study Injection

1. The participant will complete the Participant Diary daily, reporting any local or systemic reactions, daily temperature and medications taken.
2. The participant will have been instructed that if he/she experiences an AE requiring medical care, the participant should inform the study staff as soon as possible and seek medical care as appropriate. If the participant visits a health care provider, the participant should be sure to inform the health care provider of participation in this study and provide the health care provider with the investigator’s contact information.
3. Three days after second study injection (V2+3) study staff will call the participant (contact C2) to check that the participant is correctly completing the Participant Diary and to check on the participant’s well-being. If any concern arises from the safety assessment over the phone the participant will be directed to come to the study site.

### 7.2.7 Seventh Day after second Study Injection (visit S2)

1. Study staff will confirm participant identity.
2. Study staff will review the Participant Diary and interim history with the participant and inquire about any new medical events since medical histories were last updated. Any AEs that have occurred will be recorded in the appropriate CRF.
3. A study clinician will perform a targeted physical examination and record the information on the CRF. Results will be reviewed by study staff and with the participant and any AEs that have occurred will be recorded in the CRF.

Blood specimens will be collected for testing selected biochemical parameters (total bilirubin, ALT, creatinine) and selected hematologic studies (WBC, Hgb, and platelets) and for immunogenicity testing. Specimen collection information must be documented on the CRF and in specimen collection logs. About 40 mLs of blood will be collected.

Laboratory results will be reviewed by the study physician. Any out-of-normal-range result Grade 2 and above will be evaluated by the study physician to assess whether it is of clinical significance and whether it is related to vaccination. Laboratory results that are Grade 2 or above and considered to be clinically significant will be followed by the study clinician until resolution or stabilization.

The participant will be instructed to inform the study staff as soon as possible if he/she experiences an AE requiring medical care and to seek medical care as appropriate. If the participant visits a health care provider, the participant should be sure to inform the health care provider of participation in this study and give the health care provider the contact information for the investigator. Study staff may request to review any document related to participant´s visits or hospitalizations handed to study staff by participants (e.g.: hospital discharge summaries, etc), and considered relevant to the assessment of potential adverse events, and if permitted by the participant, extra information may be requested by study staff to other health care services/providers.

### 7.2.8 Second and Third weeks after second Study Injection

There are no scheduled visits during this period. Participants may be asked to come to the study clinic if the investigator follows up on any laboratory or clinical issue. The participant will inform the study clinic of any medical events and seek medical care as needed. The participant will be instructed to give any health care provider they see the contact information for the investigator.

### 7.2.9 Final Study Visit (visit I)

The visit I, schedule for day V2+28is the last in-clinic visit for the participant for collection of immunogenicity samples and review of unsolicited AE for the study.

1. Study staff will confirm participant identity.
2. A study clinician will perform a physical examination and record the information in the CRF. The results will be reviewed by the study team and with the participant and any AEs that have occurred will be recorded in the CRF
3. Study staff will review interim medical histories including any unsolicited AE and concomitant medications with the participant since these were last updated. Results will be recorded in the appropriate CRFs.
4. Blood specimens will be collected for immunogenicity testing. Specimen collection information must be documented on the CRF and in specimen collection logs. About 30,5 mLs of blood will be collected.

## 7.3 Final Study Call (contact C3)

## The contact C3 is schedule for day V2+194 and it is the last contact with the participant.

1. The participant will be contacted via telephone and identity confirmed.
2. Study staff will review interim medical histories and concomitant medications with the participant since these were last updated. No new concomitant medication will be recorded unless it relates to a newly identified SAE/AESI.
3. Study staff will ask about any medical event that would constitute an SAE since the last visit.
4. Study staff will ask if the participant has been hospitalized or had any new medically confirmed disease(s) since the last visit. Study staff will review any AESIs and report accordingly. If deemed clinically necessary, a visit to the study site will be scheduled.
5. No new AE information will be recorded unless it qualifies as an SAE or an AESI.
6. If an SAE/AESI is reported, the clinician should record the event on the appropriate form, notify the entities who require notification, and refer the participant for treatment of the SAE/AESI, if warranted. Study staff may request to review any document related to participant´s visits or hospitalizations handed to study staff by participants (e.g.: hospital discharge summaries, etc), and considered relevant to the assessment of the SAE and if permitted by the participant, extra information may be requested by study staff to other health care services/providers.
7. After recording the information, the participant will be discharged from the study.

## 7.4 Early Termination Visit

If a participant withdraws from the study for any reason prior to the planned study duration, every attempt is made to complete the following:

- Report of local and systemic reactogenicity and AEs are reviewed by PI (or designee).
- Specimens are obtained for chemistry, hematology and immunogenicity analysis if withdrawal occurs prior to scheduled safety laboratory testing.
- Participant Diary information is reviewed with the volunteer in detail by site staff, if in use since the last visit.
- Injection site(s) examination and a full physical examination are performed (if indicated).

Butantan must be informed of all instances of the premature termination of a participant’s participation in the trial.

If the participant develops a reaction to study vaccine which the investigator believes threatens the participant’s well-being, the withdrawn participant must be treated or transferred to a treatment facility.

## 7.5 Unscheduled Visits

Participants may present to the study center during operating hours for an unscheduled visit should they experience any AE, if a laboratory sample is to be repeated, or if the participant’s condition requires medical intervention. Data for any examinations or other procedures performed on the participant at an unscheduled visit must be recorded on the appropriate CRFs.

## 7.6 Termination of the Trial

### 7.6.1 End of Trial According to the Protocol

The end of the trial is defined as the date of the last visit/last phone contact of the last participant participating in the trial, according to the trial scheme.

### 7.6.2 Suspension and/or Premature Termination of the Trial

The trial or an arm of the trial can be suspended at any time by the Sponsor, any ethical review committee overseeing this study and as recommended by the DSMB for any safety concern. This includes, for example, and without limitation, an SAE resulting in death or an unusually high rate of SAEs.

# Study Evaluations

## 8.1 Clinical Evaluations

Safety evaluations will be made by a clinician on visits V1, V1+7, V2, V2+7 and V2+28 through targeted physical exams. Evaluation must be performed before and after administration of study product on V1 (day 0) and V2 (day 28). Reported signs and symptoms will be recorded by the participant on Participant Diary from Days 1-7 and Days 28-35 in the study.

### 8.1.1 Medical History

At enrollment, medical histories must be thoroughly reviewed with the participant. The following medical conditions, in particular, will be assessed:

- Current or recent (within two weeks of enrollment) acute illness with or without fever.
- Recent vaccination history.
- Recent receipt of immune globulin or other blood products, or injected or oral corticosteroids or other immune modulator therapy within 6 weeks before enrollment.
- Hypersensitivity of any kind, but particularly to vaccines.
- Asthma.
- Clinically relevant history of renal, gastrointestinal, hepatic, cardiovascular, hematological, dermatological, endocrine, neurological, or immunological diseases.
- Seizures, including history of febrile seizures, or any other neurologic disorder.
- Known or suspected immunologic impairment of any kind.
- Known HBV or HCV infection.
- Known HIV infection.
- Alcohol or illegal drug use.
- Medications currently taken.
- For women, pregnancy, menstrual and contraceptive history and/or history of surgical sterility.

### 8.1.2 Physical Examination

General Physical Examinations

Qualified study clinicians will conduct a physical examination of all participants at screening. This physical examination will include the following:

- Recording of general appearance
- Height and weight (only needed at one screening visit)
- Targeted physical examination
- Measurement of the following vital signs:
  - body temperature (and body location of measurement)
  - blood pressure
  - pulse and/or heart rate

*Out-of-range observations may not be considered to be exclusionary at screening nor an adverse event (AE) for the study, unless judged to be clinically significant by the PI.

## 8.2 Laboratory Evaluations

### 8.2.1 Clinical Laboratory Evaluations

All biochemical and hematological testing will be performed at a laboratory associated with the study sites in Brazil. The laboratories should follow GLP standards.

Laboratories will follow written procedures for conducting all laboratory assays.

Normal value ranges will be considered according to each clinical laboratory conducting tests. A Toxicity Table for Grading AEs, including out-of-range laboratory values, is included in section 9.3.

A laboratory result that is out-of-range but no greater than Grade 1 does not qualify as an AE and does not require determination of clinical significance or relatedness to the study products. A result will be checked as not clinically significant “NCS” on the laboratory result CRF if it is outside the lab range but lower than Grade 2.

Serology for Viral Infections (Screening only)

Blood specimens will be evaluated for the following using tests routinely used in the laboratories:

- Hepatitis B virus surface antigen (HBsAg)
- HCV antibody using anti-HCV test
- HIV serology testing

Specimen collection will occur on Day of screening. Pre and post-test counseling will be offered to participants according to protocols of the Brazilian Ministry of Health. Likewise, patients who test positive for any of the serological tests will be referred for appropriate prevention, treatment and care services. There will be coordination with laboratory services to support quality assurance and delivery of correct results. Determinant results of a participant’s testing must be obtained from the laboratory and evaluated prior to administration of any study product.

Pregnancy Test

In order to confirm pregnancy status of females, a qualitative human chorionic gonadotropin (hCG) test will be done on a urine sample collected on Day of Screening and before each study injection. No injection of study product may be given to a woman without a pregnancy test being done and to any woman with a positive pregnancy test.

Blood Chemistry and Hematology

Specimen collection will occur on visits T, S1, V2 e S2. Results of testing for the participant will be reviewed by a study physician. Considering the tests of visits S1 and S2, out-of-range results Grade 2 and above will be assessed for clinical significance and relatedness to study injection and repeated. Any results that are Grade 2 or above and clinically significant should be followed until normal or stabilized prior to termination of participant participation in the study. “Clinically significant” means the result warrants further medical investigation or treatment because it may have impact on a person’s health status. If the clinician is unsure of clinical significance, the specimen should be re-drawn and the test re-run.

Blood Chemistry

- Creatinine
- Alanine aminotransferase (ALT, also called SGPT)
- Aspartate aminotransferase (AST, also called SGOT)
- Total bilirubin

Hematology

- Number of WBC and differentials
- Hemoglobin (Hgb)
- Hematocrit (Hct)
- Platelet count

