| Review and collect participant diary | | | | | |  | | |  | | |  | | X | |  | | |  | | X | |  | | |  |  |
| **Safety evaluation** |  | | |  | | |  | | | |  | | | |  | | |  | | | |  | | |  | | |
| Urine β-hCG ^†^ | | | | | | X | | | X | | |  | |  | | X | | |  | |  | | X | | |  |  |
| Collect blood sample for HBV, HCV and HIV testing | | | | | | X | | |  | | |  | |  | |  | | |  | |  | |  | | |  |  |
| Collect blood sample for hematology | | | | | | X | | |  | | |  | | X | |  | | |  | | X | |  | | |  |  |
| Collect blood sample for biochemical testing | | | | | | X | | |  | | |  | | X | |  | | |  | | X | |  | | |  |  |
| **Immunogenicity evaluation** | |  | | |  | | |  | | | | |  | | | |  | | |  | | | |  | | |  |
| Collect blood sample for anti-influenza serologic testing | | | | | |  | | | X | | |  | |  | | X | | |  | | X | | X | | |  |  |
| **Volume of blood collected (ml)** | |  | | |  | | |  | | | | |  | | | |  | | |  | | | |  | | |  |
| Total volume | | | | | | **17,5** | | | **30,5** | | | **-** | | **9** | | **39,5** | | | **-** | | **39,5** | | **30,5** | | | **-** |  |

^†^ For womem at risk of pregnancy

Research Protocol

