### 8.2.3 Preparation, Processing and Specimens

Blood Specimens

Blood will be collected according to universal precautions for testing in multiple assays. Serum for the following: blood chemistry, HBV, HCV and HIV serology, HI antibody serology. Whole blood is collected for WBC, Hgb, Hct, and platelets.

|  | **Volume of blood** | **Day of Screening** | **V1**  **(pre-vac)** | **S1** | **V2**  **(pre-vac)** | **S2** | **I** |
| --- | --- | --- | --- | --- | --- | --- | --- |
| Whole blood for Hematology | 4 mL | ✓ |  | ✓ | ✓ | ✓ |  |
| Serum for serology for HBV, HCV and HIV infection | 8,5 mL | ✓ |  |  |  |  |  |
| Serum for biochemical parameters | 5 mL | ✓ |  | ✓ | ✓ | ✓ |  |
| Serum for anti-influenza serologic assays | 30,5 mL |  | ✓ |  | ✓ | ✓ | ✓ |

(The total volume of blood planned to be collected from each participant during the course of the study will be less than 170 milliliters.)

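### The safety laboratory schedule contradicts itself: section 7.2.7 drops AST from the only chemistry sample after dose 2, and the V2 laboratories are required in some places and absent in others

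*Protocol*

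**What the plan says.** **Chemistry panel.** Section 8.2.1 lists creatinine, ALT, AST and total bilirubin, without distinguishing visits. Section 7.2.3 names the same four tests at S1. Section 7.2.7 names three at S2, without AST. Table 5 grades ALT and AST in one row, and it uses their status to choose between two bilirubin scales.

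**Visits.** For blood chemistry and haematology, section 8.2.1 states "Specimen collection will occur on visits T, S1, V2 e S2". The table in 8.2.3 ticks "Whole blood for Hematology" (4 mL) and "Serum for biochemical parameters" (5 mL) at screening, S1, V2 before vaccination, and S2.

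Table 1 in the Protocol Summary marks "Collect blood sample for hematology" and "Collect blood sample for biochemical testing" at T, S1 and S2 and leaves both blank at V2. Its volume row nevertheless gives 39.5 mL at V2, the same as at S2.

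Section 7.2.5 describes the V2 draw thus: "a blood specimen will be collected by venipuncture from the participant for immunogenicity testing". It then adds "About 40 mLs of blood will be collected". For V1, where only influenza serology is drawn, section 7.2.1 says "About 30 mLs of blood will be collected".

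Section 4 names biochemical and haematological tests at S1 and S2. For V2 it names only immunogenicity or immunological testing.

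**The concern.** These are collection instructions in a first-in-human study of the antigen and adjuvant combinations, planned for at least three sites. Where they conflict, two sites can each comply and still hold different safety data.

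The AST omission carries more weight. S2 is the only scheduled chemistry sample after the second injection. The laboratory halting rules in section 9.6 cover the 7 days after each injection and count severe abnormalities in the same parameter. A site following 7.2.7 alone would supply no AST result for that count after dose 2. It could also assign bilirubin a lower grade than Table 5 intends.

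The V2 conflict decides whether one safety sample, the only one scheduled between S1 and S2, is taken at all.

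**Working it through.** **1. AST, by section**

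| Source | S1 | S2 |
|---|---|---|
| 8.2.1 panel | yes | yes |
| 7.2.3 (S1) and 7.2.7 (S2) | yes | no |

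Scheduled AST after dose 2: 1 under 8.2.1, 0 under 7.2.7. The haematology lists in 7.2.3 and 7.2.7 are identical (WBC, Hgb, platelets). AST is the only test on which the two visit lists differ, and no reason is given.

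**2. Effect on bilirubin grading (Table 5)**

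Take a participant with normal ALT and raised AST:

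| Bilirubin, x ULN | Grade if the AST rise is known | Grade if only the normal ALT is seen |
|---|---|---|
| 1.7 | 3 (range 1.51 to 1.75) | 2 (range 1.6 to 2.0) |
| 1.8 | 4 (above 1.75) | 2 (range 1.6 to 2.0) |

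Grades 3 and 4 count towards the laboratory halting rules and Grade 2 does not. So a missing AST can affect a second parameter. These bilirubin values are illustrations; the protocol does not say how often such a pattern would occur.

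**3. Blood volumes at V2**

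Inputs from the 8.2.3 table: haematology 4 mL, chemistry 5 mL, viral serology 8.5 mL, influenza serology 30.5 mL.

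Reproducing Table 1's volume row from the 8.2.3 ticks:

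- T: 4 + 8.5 + 5 = 17.5 mL
- V1: 30.5 mL
- S1: 4 + 5 = 9 mL
- V2: 30.5 + 4 + 5 = 39.5 mL
- S2: 30.5 + 4 + 5 = 39.5 mL
- I: 30.5 mL

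Total: 17.5 + 30.5 + 9 + 39.5 + 39.5 + 30.5 = 166.5 mL. Every visit agrees with Table 1, and the total is below the 170 mL limit in 8.2.3.

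Using only the procedures that Table 1 marks at V2, the draw there is 30.5 mL and the total is 166.5 − 9 = 157.5 mL. That disagrees with Table 1's own 39.5 mL and with the roughly 40 mL in 7.2.5. Table 1 is therefore inconsistent within itself.

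**4. Is the blank at V2 an extraction fault?**

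Aligned cell by cell with the visit header, both safety rows have marks at T, S1 and S2 and an empty cell at V2. In the same table the influenza serology row does carry a mark at V2. The blank belongs to the table.

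**The case against.** **On AST.** Both visit lists are short parenthetical selections, and both also leave out haematocrit and the WBC differential that 8.2.1 includes. The 8.2.1 panel still applies to S2, ALT is listed there, and Table 5 puts ALT and AST in one row. This looks like a dropped word. That is fair as far as it goes: a reader might infer that liver monitoring after dose 2 is lost, and it is not. What stands is that an isolated AST rise could be missed at a site working from 7.2.7, with the bilirubin consequence shown above.

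**On V2.** A reader might infer that dose 2 would be given without a required safety check, or that a halting signal would be lost. The text supports neither. V2 lies outside the 7-day halting window, nothing makes dose 2 conditional on the V2 result, and the laboratory exclusion in section 5.3 concerns screening values. A reader might also infer that V2 results would go unassessed, because the sentence in 8.2.1 on assessing and repeating results names only S1 and S2, or unanalysed, because 11.5 mentions Days 7 and 35. But 9.3.1 and 9.3.8 require any Grade 2 or higher result to be assessed, and the wording in 11.5 is inclusive.

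**On direction.** The volumes are not independent proof that V2 laboratories were meant. They may all repeat one ticked cell in 8.2.3. The Table 1 marks, 7.2.5 and section 4 point the other way. Deleting V2 would also resolve the conflict. This objection stands: the intention is an inference, though a well-supported one.

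**On mitigation.** Section 13 provides for guiding data collection forms and mandatory training. These lower the risk of uneven collection without removing it.

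**Conclusion.** The protocol contradicts itself on two separate matters, and they should be sized separately.

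- **AST at S2 (main point).** Scheduled AST after dose 2 is 0 under 7.2.7 and 1 under 8.2.1. This bears on the halting rule counted by parameter and on bilirubin grading. It assumes that a site follows the visit section literally.
- **Laboratories at V2 (lesser point).** 9 mL of safety blood per participant is taken or not, depending on the section followed. The cost is uneven data between sites. Neither the halting rules nor the second injection depends on this sample.

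A reader might add the two together and say AST falls from three measurements after the first injection to one. That mixes an omitted test with a disputed visit and overstates the AST problem, which is a single visit.

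No endpoint definition, planned analysis, sample size or power is affected. The correction is worth making because these are operative safety instructions and it costs almost nothing.

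**What to change.** 1. Add AST to the S2 chemistry list in 7.2.7. No extra tube is needed, since 5 mL is already drawn for chemistry at S2.
2. Reconcile V2. The preferred route is to mark haematology and biochemistry at V2 in Table 1 and to name them in 7.2.5 and in the V2 paragraph of section 4. The explicit statements in 8.2.1 and 8.2.3 and all the stated volumes support this, and the total stays at 166.5 mL.
3. If V2 laboratories were not intended, remove V2 from 8.2.1 and its two ticks from 8.2.3. Also lower the V2 volume to 30.5 mL in Table 1 and to about 30 mL in 7.2.5. The total becomes 157.5 mL.
4. Optional, if V2 stays: add V2 to the sentence in 8.2.1 on assessing and repeating results, and Day 28 to 11.5. Both only clarify, since 9.3.1 and 9.3.8 already require assessment.

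The cost is wording only, with no additional blood beyond what is already planned.
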